### Participants

Study participants will include individuals who have abstained from smoking during the last month while undergoing standard smoking cessation therapy (3 months after the initial visit).

### Inclusion criteria

Individuals who have abstained from smoking during the last month while undergoing standard smoking cessation therapy (3 months after the initial visit) and fulfilling the following will be included: (1) individuals who do not exercise (those who do not answer “I have continued to exercise 30 min a day at least twice a week for over a year” in a questionnaire); (2) age 20–75 years; and (3) individuals who agree to the purpose of this study and who provide written consent.

### Exclusion criteria

Individuals fulfilling any of the following items will be excluded: (1) those prohibited from exercising by their physician (individuals for whom exercise is contraindicated); (2) those who would have difficulty exercising due to conditions, such as an orthopedic disorder, neuromuscular disease, or peripheral vascular disease; (3) pregnant women; (4) in-patients or residents of a facility; or (5) individuals whose participation in this study has been deemed inappropriate by their primary physician.

### Discontinuation criteria

This study will be discontinued in the event of any of the following: (1) continuation of the study is not feasible due to adverse events; (2) the study cannot be continued due to participant withdrawal or withdrawal of consent; (3) participants meet the exclusion criteria or are deemed ineligible after enrollment; (4) women who are pregnant; (5) marked noncompliance; (6) the study itself is discontinued; or (7) an investigator otherwise deems that continuing this study is not feasible.

### Ethical considerations

All procedures will be carried out in accordance with the ethical standards of the facilities involved and those of domestic research councils and in accordance with the 1964 Helsinki Declaration and its subsequent amendments or comparable ethical standards.

### Study protocol

An overview of the proposed study protocol is shown in Fig. 1. The schedule of enrollment, interventions, and assessments is shown in Fig. 2. The Standard Protocol Items: Recommendations for Interventional Trials (SPIRIT) Checklist is provided in Additional file 1.

**Fig. 1 Fig1:**
[figure not shown]
Overview of study protocol

**Fig. 2 Fig2:**
[figure not shown]
Schedule of enrollment, interventions, and assessments

### Allocation

Participants will be centrally allocated using the electronic data capture (EDC) system of the University Hospital Medical Information Network. After written consent is obtained from participants who meet the selection criteria, the lead investigator will verify that the participants meet all of the eligibility criteria and none of the exclusion criteria, and their information will be registered in the EDC system. After registration, the EDC system will assign patient numbers that do not include a patient’s personal information. Immediately after entry, the EDC system will randomly assign participants to one of two groups (exercise intervention or control groups) by dynamic allocation.

### Allocation and allocation adjustment factors

Potential confounding factors (age, sex, number of cigarettes smoked per day, Fagerstrom test for nicotine dependence (FTND) score, and self-rating depression scale (SDS) score) will be adjusted between the two groups via registration in the EDC system. Participants will be randomized by minimization, which is a method of dynamic allocation.

### Intervention

#### Acquisition of data at the beginning of the study

Patient characteristics (sex, age, medical history, history of present illness, alcohol consumption, type of medications taken, and psychological state), blood chemistry measurements (white blood cell count, red blood cell count, hemoglobin, hematocrit, platelet count, fasting blood glucose, total cholesterol (T-cho), high-density lipoprotein cholesterol (HDL-cho), and triglyceride (TG)), and measurements of height, weight, blood pressure, and concentration of exhaled carbon monoxide will be examined at the beginning of the study. Smoking status (number of years of smoking, number of cigarettes smoked, tobacco dependence screener score, FTND score, age the individual started smoking, smokers in the family, and number of previous attempts to quit smoking) will be recorded during an interview at the initial visit to the smoking cessation clinic.

#### Exercise intervention group

After completion of the smoking cessation therapy, participants will be informed of the significance of active exercise while attempting to quit smoking. Participants will receive an activity tracker for the duration of the study and will be instructed on exercises to increase and maintain their physical activity as part of their daily lives.

#### Setting of exercise goals

During follow up, participants will individually record their daily step count, level of activity, and weight. Participants will be regularly followed up approximately 2–4 times over 9 months. During regular follow up, participants will receive feedback based on their individual logs, their exercise goals will be adjusted, and they will be encouraged to maintain their amount of physical activity and control their weight. Exercise instruction will be provided in accordance with an exercise instruction manual compiled under the supervision of a certified fitness instructor and a certified cardiac rehabilitation specialist.

#### Standard therapy (control) group

The control group will be followed during the course of the standard smoking cessation program. After completing smoking cessation therapy, participants will not be actively advised to exercise; therefore, further exercise instruction will not be provided.

Participants will receive an activity tracker immediately after completing smoking cessation therapy and 8 months after beginning the study. They will return the tracker 1 month later in both instances. Participants will be regularly followed up 2–4 times over 9 months. During regular follow up, we will confirm whether smoking cessation has continued, and participants will not receive active instructions for exercise.

#### Data collected during the study and follow-up periods

The study will begin on the day the participant is given an activity tracker. The follow-up period will be 9 months in both groups. In addition to face-to-face meetings, follow up may be conducted by mail, telephone, or on line. Participant status will be ascertained at the beginning of the study and at 1, 8, and 9 months after beginning the study. Continuous abstinence from smoking, psychological state, type of medications taken, blood chemistry measurements (white blood cell count, red blood cell count, hemoglobin, hematocrit, platelet count, fasting blood glucose, and T-cho, HDL-cho, and TG), and measurements of height, weight, blood pressure, and concentration of exhaled carbon monoxide) will be assessed in both groups after 9 months.

#### Items observed and studied

Primary endpoint: the primary endpoint will be continuous abstinence rate. An individual is deemed to have continuously abstained from smoking if they report when interviewed that they have not smoked in the past week and if their concentration of exhaled carbon monoxide is ≤ 7 ppm [12].

Secondary endpoints: the secondary endpoints are changes in metabolic indices (height, weight, blood pressure, exhaled carbon monoxide concentration, red blood cell count, white blood cell count, hemoglobin, hematocrit, platelet count, fasting blood glucose, T-cho, HDL-cho, and TG) and changes in an individual’s psychological state (SDS score, depressive tendencies, and patient activation measure score).

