## Study objective

The present study aims to determine the effects on continuous abstinence from smoking of exercise instruction provided after completion of 12-week smoking cessation therapy (covered by the national health insurance).

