### Analysis

#### Analysis set

The two groups (exercise intervention and control groups) will be compared based on the intention-to-treat principle. All data for the metabolic indices and psychological states of the participants in each group obtained upon enrollment and 9 months after enrollment will be analyzed. Individuals who quit smoking for a prolonged period will be similarly analyzed and those who resume smoking will be excluded. Quitting smoking for a prolonged period is defined as not smoking for 9 months after enrolling in the study (determined by interview) and having exhaled carbon monoxide levels ≤ 7 ppm. The continuous abstinence rate is defined as the proportion of participants who abstain from smoking with respect to the total number of participants in each group.

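### The primary endpoint is named continuous abstinence but scored on the past week, and its time window is not consistent across the protocol

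*Protocol article*

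**What the plan says.** The Study objective is to "determine the effects on continuous abstinence from smoking of exercise instruction provided after completion of 12-week smoking cessation therapy". Under Items observed and studied, "the primary endpoint will be continuous abstinence rate". The criterion follows at once: "An individual is deemed to have continuously abstained from smoking if they report when interviewed that they have not smoked in the past week". The same sentence adds a breath-test condition, an exhaled CO of at most 7 ppm.

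The Analysis set section introduces another term. "Individuals who quit smoking for a prolonged period will be similarly analyzed and those who resume smoking will be excluded". It then explains what it means by that term: "Quitting smoking for a prolonged period is defined as not smoking for 9 months after enrolling in the study (determined by interview"), with the same CO cut-off. The next sentence returns to the primary measure: "The continuous abstinence rate is defined as the proportion of participants who abstain from smoking with respect to the total number of participants in each" of the two arms. It gives no period over which a participant must abstain.

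On timing, the section on data collected during follow-up says: "Participant status will be ascertained at the beginning of the study and at 1, 8, and 9 months after beginning the study". Continuous abstinence and CO are assessed after 9 months. The control-group section also has staff check at regular follow-up that cessation has held.

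**The concern.** Everyone enrolled has already abstained for a month, so the event of interest is a return to smoking during the following 9 months. A rule that looks back one week does not register a relapse that ended before that week. The CO criterion does not close the gap: it belongs to both definitions, and at month 9 it says nothing about the earlier months. Status is collected at months 1 and 8, but the primary criterion makes no use of it.

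At stake is what the headline result means. A reader told that continuous abstinence improved would take it to mean no smoking throughout, whereas the rule as written reports status at one point in time. If relapse followed by renewed quitting is common, or differs between arms, the two measures can give different answers.

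**Working it through.** **1. The definitions side by side**

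| Section | Term | Self-report window | CO | Used for |
|---|---|---|---|---|
| Items observed and studied | Continuously abstained | Past week | ≤ 7 ppm | Primary endpoint |
| Analysis set | Quitting for a prolonged period | 9 months from enrolment | ≤ 7 ppm | Subset for the secondary indices |
| Analysis set | Continuous abstinence rate | None given | Not mentioned | Primary rate, all participants in the group |

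Take a participant who smokes from month 2, stops ten days before the month-9 interview and has CO ≤ 7 ppm. The first row makes this person a primary success. The second row removes the same person from the abstainer subset. The third row does not decide.

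**2. The planned sample size**

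Inputs from Sample size: control rate 50%, odds ratio 2, power 0.80, α 0.05 (two-sided, from Items analyzed and analytical methods).

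- Exercise rate: odds 2 × (0.5/0.5) = 2, so 2/3 = 66.7%.
- Unpooled two-proportion formula: n = (1.960 + 0.842)² × (0.5 × 0.5 + 0.667 × 0.333) / (0.167)² = 133.4, so 134 per group. This matches the protocol.
- Dropout: 134/0.9 = 148.9, so 149, which the protocol rounds to 150.

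**3. Illustration A: the planned rates are sustained-abstinence rates**

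Let r be the share of 9-month failures in each arm who pass the past-week rule. The documents give no value for r, so 10–30% is an assumption. The observed rate in an arm is p + r(1 − p), so the difference is multiplied by (1 − r). Power is for the two-sided Fisher exact test at 150 per group, by full enumeration, with an outcome for everyone.

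| r | Control | Exercise | Difference (points) | Power |
|---|---|---|---|---|
| 0 | 50% | 66.7% | 16.7 | 81% |
| 10% | 55% | 70.0% | 15.0 | 73% |
| 20% | 60% | 73.3% | 13.3 | 65% |
| 30% | 65% | 76.7% | 11.7 | 56% |

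**4. Illustration B: the odds ratio of 2 holds on the past-week outcome**

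The control rates are as above. The exercise rate is o/(1 + o), with o = 2 × control odds.

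| Control | Exercise | Power |
|---|---|---|
| 55% | 71.0% | 79% |
| 60% | 75.0% | 76% |
| 65% | 78.8% | 72% |

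**5. Unequal r**

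With the planned rates as sustained rates, r = 10% in control and 20% in exercise gives 55% v 73.3%, a difference of 18.3 points. The reverse gives 60% v 70%, a difference of 10 points. The contrast can move either way.

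**The case against.** The best defence is that only one passage sets a criterion under the label of primary endpoint, and that is the past-week rule. The 9-month definition belongs to a different term and forms a subset for metabolic and psychological indices. This is correct. A reader might infer that the protocol holds two rival primary definitions, so that a convenient one could be picked after the data are seen, or that the relapser above is scored a primary failure in the Analysis set section. The text says neither. What remains is that the rate is restated without a window directly after a 9-month standard, and that the one explicit rule does not fit its name.

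Second, because all participants are abstinent at entry, anyone smoking at month 9 has resumed. A CO-verified status at month 9 therefore measures net resumption. It would be wrong to say that it does not bear on the objective; it misses only relapse followed by renewed quitting.

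Third, a reader might infer that the endpoint does not match the sample size, because the Background gives a continuous abstinence rate of about 50% at 1 year. The Sample size section neither cites that figure nor defines success. The Background's fall from about 70% at the end of treatment to about 50% may also rest on all treated patients. If so, the rate among people already abstinent would be nearer 50/70 = 71%. The link is an inference, and the power figures are conditional on it.

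**Conclusion.** The point holds as a fault in the stated rule, not as an omission that a fuller document would cure. The primary endpoint is called continuous and scored as 7-day point prevalence, so some participants who relapsed are counted as continuously abstinent. The window for the primary endpoint is also not consistent across the document.

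The size cannot be fixed from the documents. Power at 150 per group falls from 81% to 73–56% if 10–30% of relapsers in both arms pass the past-week rule and 50% v 66.7% are sustained rates. It falls to 79–72% if the odds ratio of 2 applies to the past-week outcome. Neither range shows that 134 per group, or 300 in total, is wrong. The figure reproduces, and it stands if the planning rates describe sustained abstinence.

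**What to change.** Use one definition of the primary endpoint in both Items observed and studied and Analysis set: no smoking from enrolment to month 9 by interview, drawing on the status already ascertained at months 1, 8 and 9, with CO ≤ 7 ppm at month 9, over all randomised participants. State how a missed month-1 or month-8 contact is handled. Keep past-week abstinence with CO as a secondary endpoint, named 7-day point prevalence.

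Recruitment is ongoing and the trial is open-label, so this is a change to a primary endpoint and more than an edit of wording. It should be dated and documented before any outcome is compared by arm.

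The cost is small in data collection: the contacts, the CO test and a 9-month interview determination are already planned. The downside is a lower abstinence rate in both arms, by an amount that the documents do not allow to be estimated.

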### Analysis

#### Analysis set

The two groups (exercise intervention and control groups) will be compared based on the intention-to-treat principle. All data for the metabolic indices and psychological states of the participants in each group obtained upon enrollment and 9 months after enrollment will be analyzed. Individuals who quit smoking for a prolonged period will be similarly analyzed and those who resume smoking will be excluded. Quitting smoking for a prolonged period is defined as not smoking for 9 months after enrolling in the study (determined by interview) and having exhaled carbon monoxide levels ≤ 7 ppm. The continuous abstinence rate is defined as the proportion of participants who abstain from smoking with respect to the total number of participants in each group.

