### Exercise can inhibit weight gain after quitting smoking

Weight gain typically occurs after smoking cessation. A recent meta-analysis reported that people on average gain 4.7 kg in weight 1 year after quitting smoking [10]. Weight gain after smoking cessation may lead to the resumption of smoking, and preventing weight gain is a vital aspect of smoking cessation support. Japanese smoking cessation programs using drug therapy provide instruction primarily in the form of diet and cognitive behavioral therapy; however, several studies have reported that such programs may not result in adequate weight control [11, 12]. Explaining specific forms of exercise to individuals who are attempting to quit smoking and do not exercise may help to improve the success rate for quitting smoking and help manage subsequent weight control.

Several intervention studies have examined the effects of combining exercise instruction with drug therapy. In a systematic review of 20 studies (including 5870 participants) examining the effectiveness of exercise interventions, the largest of the 20 studies was an Internet trial of 2318 individuals. Of the 20 studies, 8 had fewer than 30 subjects, 9 included only women, and 1 included only men. Although 4 of 20 studies reported adequate sample size and the effectiveness of exercise in smoking cessation, the effect of exercise instruction on smoking cessation remains unclear [13].

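### The supplementary comparison of secondary endpoints in prolonged quitters only is not a randomised comparison and should carry no between-arm inference

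*Protocol article*

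**What the plan says.** All references are to the protocol article.

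- **Full set.** Analysis set states that the two arms "will be compared based on the intention-to-treat principle". It continues: "All data for the metabolic indices and psychological states of the participants in each group obtained upon enrollment and 9 months after enrollment will be" analysed.
- **Restricted set.** The next sentence reads: "Individuals who quit smoking for a prolonged period will be similarly analyzed and those who resume smoking will be excluded". Membership requires no smoking over the nine months after enrolment, established by interview, and exhaled carbon monoxide of 7 ppm or less.
- **Endpoints.** Items observed and studied states that "the primary endpoint will be continuous abstinence rate" and that "the secondary endpoints are changes in metabolic indices", together with changes in psychological state.
- **Tests.** Items analyzed and analytical methods compares those changes between the arms by t test or Wilcoxon rank-sum test, allows regression adjustment, and sets significance at p ≤ 0.05.
- **Link between outcomes.** The background section on weight says: "Weight gain after smoking cessation may lead to the resumption of smoking".

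The natural reading of similarly is that the same between-arm tests are run again in quitters only.

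**The concern.** Whether a participant stays abstinent is known only after randomisation, and it is in substance the primary endpoint. Items observed and studied words abstinence as no smoking in the past week, while the restricted set uses nine months. Under either wording it is an outcome that the intervention is meant to move.

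If exercise works as hoped, it keeps in the restricted set some people who would have relapsed under control. The quitters in the two arms are then different mixtures of people. Where a secondary outcome is related to relapse, the arms can differ on it without any effect of exercise, or a real effect can be hidden. The protocol states such a link for weight. It also says, in the section on exercise and quitting, that stress relief helps curb resumption, so the psychological endpoints are open to the same problem.

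At stake is how the quitter-only weight, mood and laboratory results are read. With the same tests and significance level as the full-set comparison, they would look like randomised evidence of an exercise effect.

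**Working it through.** **Inputs from the protocol (Sample size).** Control abstinence 50%; odds ratio 2; two-sided α 0.05; power 0.8; 134 per group; 150 per group after 10% dropout.

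**Reproducing the plan's figure.**
- Control odds are 1, so exercise odds are 2 and the exercise rate is 2/3 = 66.7%.
- With unpooled variance, n = (1.960 + 0.842)² × (0.5 × 0.5 + 0.667 × 0.333) / (0.1667)² = 7.849 × 0.4722 / 0.02778 = 133.4, that is 134 per group.
- 134 / 0.9 = 148.9, or 149, which the plan rounds to 150.

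The sample size is sound, and the two rates can be used below.

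**Size of the restricted set.**
- Of 150 per arm: 150 × 0.5 = 75 controls and 150 × 0.667 = 100 exercise participants remain. Excluded: 75 + 50 = 125 of 300 (42%), made up of 50% of controls and 33% of the exercise arm.
- Of 134 evaluable per arm: 67 and about 89 remain.

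**Selection with no true effect.** Suppose a secondary outcome, in SD units, has correlation ρ with a normally distributed liability to relapse. Exercise shifts only the proportion who relapse and has no effect on the outcome. If a fraction q is retained, with z = Φ⁻¹(q), the mean among those retained moves by −ρ × φ(z)/q.
- Control, q = 0.5: φ(0)/0.5 = 0.798.
- Exercise, q = 0.667: φ(0.431)/0.667 = 0.545.
- Spurious arm difference: (0.798 − 0.545) × ρ ≈ 0.252ρ.

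The protocol gives no value for ρ, so it is an assumption shown over a range. False-positive rates come from a simulation of 20,000 runs per setting with 134 per arm.

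| Assumed ρ (absolute value) | Spurious difference | False-positive rate, quitters only | False-positive rate, all participants |
|---|---|---|---|
| 0 | 0 | about 5% | about 5% |
| 0.2 | 0.05 SD | about 6% | about 5% |
| 0.3 | 0.08 SD | about 8% | about 5% |
| 0.5 | 0.13 SD | about 13% | about 5% |

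**Higher retention.** Participants have already quit when enrolled. The background section on long-term effectiveness gives about 70% success at the end of treatment and about 50% at one year, so retention among those already abstinent could be 50/70 = 71.4%. The odds are then 2.5; doubled they are 5, giving 5/6 = 83.3% with exercise. The same formula gives differences of 0.035, 0.053 and 0.088 SD for ρ of 0.2, 0.3 and 0.5. About 23% of participants are excluded: (28.6% + 16.7%) / 2.

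**Direction.** If greater weight gain leads to relapse (ρ positive), the more heavily selected control quitters look lighter, and a benefit of exercise is partly hidden. If relapsers gain less weight because they smoke again (ρ negative), the sign reverses and a benefit is mimicked. The two may partly cancel.

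**Precision.** The difference detectable with 80% power is √(7.849 × 2/134) = 0.34 SD in the full set and √(7.849 × (1/67 + 1/89.3)) = 0.45 SD in quitters.

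**The case against.** The strongest reply is that the randomised comparison is kept. The quitter-only analysis follows the intention-to-treat statement as an addition, and the primary endpoint uses every participant in each group as its denominator. That is right. A reader might infer that intention-to-treat has been abandoned for the secondary endpoints, or that the primary result is affected; the text supports neither.

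A reader might also infer that weight control is a formal aim and that the quitter-only result would be headlined. The Study objective names abstinence alone, weight gain appears as an intended use of the findings in the abstract's discussion, and weight is one of many secondary measures. That the restricted result would be reported as the main one is speculation.

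The ranking and labelling of supplementary analyses may sit in a fuller document, so the lack of a stated order is not held against the plan. What remains is a stated instruction to repeat the comparison in a set chosen by outcome.

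Two further replies stand in part. Weight change after quitting is naturally a question about people who stay quit, so the restricted results are worth showing. Regression adjustment can reduce imbalance in measured baseline factors, but it does not reliably remove selection that works partly through changes after baseline.

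**Conclusion.** The concern holds for the supplementary quitter-only contrast and goes no further. That contrast does not have the protection of randomisation if exercise changes abstinence, which is the trial's own hypothesis.

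The likely distortion is modest: about 0.05 to 0.13 SD at the planned rates and 0.035 to 0.088 SD at the higher retention, for ρ between 0.2 and 0.5. These figures rest on an assumed ρ and a normal selection model. The direction cannot be fixed from the protocol, and the model gives no bias if exercise leaves abstinence unchanged or if the outcome is unrelated to relapse. The wording should be changed because the change is cheap and the misreading avoidable; the validity of the trial's main conclusions is not in doubt.

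**What to change.** In Analysis set, state that between-arm inference on every secondary endpoint uses all randomised participants with data, regardless of smoking status. Replace the sentence that excludes those who resume smoking with one saying that results in prolonged quitters are shown by arm as supplementary, descriptive and non-randomised, and that no exercise effect will be claimed from them.

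The cost is wording only, with no extra data or participants. The downside is that the all-randomised weight comparison mixes quitters with relapsers, so it does not isolate weight change in those who stay quit. The descriptive table still shows that group.
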